### Assessments and procedures

Baseline assessments will be administered to all participants through an online survey by the research team. Questionnaires include PHQ-9, MSPSS, WHO-5 and socio-demographics. These questionnaires will be translated into the local languages and back-translated for accuracy. Detailed instructions and sufficient explanations will be provided on the initial page of the online survey.

The PHQ-9 questionnaire will be used to measure depression, with scores of 1–4, 5–9, 10–14, 15–19 and 20–27 indicating minimal, mild, moderate, moderately severe and severe depressive symptoms. WHO-5 questionnaire will measure mental wellbeing and the total row score (ranging from 0 to 25) is multiplied by 4 to provide the final score. 0 represents the worst possible mental wellbeing, and 100 represents the best possible mental wellbeing. The MSPSS will be used to measure perceived social support from three sources: family, friends and a significant other. This measure contains 12 questions which rated on a 7-point scale as ‘very strongly disagree’, ‘strongly disagree’, ‘mildly disagree’, ‘neutral’, ‘mildly agree’, ‘strongly agree’ and ‘very strongly agree’.

Post-intervention follow-up assessment will be carried out through telephone for both control and intervention arm. This will use the same baseline survey assessment tools and will be performed online. The outcome assessors are professionals trained in research methodology and are specifically skilled in data collection and management.

### Training of the staff

The expert resource persons will train the chief executive officer and the chief operating officer/state programme manager from the six selected PIAs (12 in total) on the intervention manual’s content, process and strategies. Training of trainers will be given to 36 facilitators, six members each from 6 intervention PIAs and the State Rural Livelihood Mission (SRLM) from the selected states. A virtual master class will train these facilitators on providing the intervention (telephonic befriending). This training will last for approximately 6 h and will include a session on question and answers. Following this training, the training video, protocol booklet and frequently asked Q&As will be shared with the facilitators. Additionally, an online support centre will be set up for continuous support to the trainers.

The trained facilitators will train 6 PIA staff (two from each agency) and each trained PIA staff will train an average of 6 other staff members. Staff who are a part of the DDU-GKY project for 1 year or longer will be trained to deliver the intervention. Staff who are a part of the intervention team will only receive this training on the intervention module. These trained staff members will reach out to 720 DDU-GKY alumni through this intervention.

Each befriender will be allocated between 10 and 15 students in their PIA. A 6-h virtual training is designed for the staff, covering the components to be delivered during each session. An intervention manual for the training has been developed, which was also translated into the local language. After the training, the trained staff will be provided with the intervention manual, an online video of the training session with subtitles, audio clips of sample interview content and a module on frequently asked questions. The intervention manual includes guidelines on developing a relationship with the client, introduction and orientation of participant to befriending, management of participant distress, confidentiality and safety issues for both staff and participants. In addition to the virtual training, befrienders will be monitored frequently through the online support centre to ensure fidelity to the intervention protocol.

Separate staff members will be involved in the intervention arm and control arm. No specific training will be given for the staff making the telephonic calls in the control arm. They will provide general information about the precautions necessary to protect themselves from the infection and inquire about how the family is coping with the lockdown related issues.

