#### Control arm: general enquiry phone calls

Participants randomised to the control arm will not be receiving any intervention. However, they will participate in a baseline and follow-up assessment using the same instruments. They will receive four general enquiry phone calls lasting 5 to 30 min. It will be a general inquiry about the precautions that are necessary to protect themselves from the infection, and how the family is coping with the lockdown-related issues. The main focus will be given on psycho-education-based inquiries on COVID-19.

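### Control callers get no specific training, and the only distress guidance the article describes goes to intervention callers; one shared page would be a cheap safety improvement

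*Protocol article*

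**What the plan says.** The statements are in the protocol article, mostly under Training of the staff.

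- **Control callers:** "No specific training will be given for the staff making the telephonic calls in the control arm". They give information on infection precautions and "inquire about how the family is coping with the lockdown related issues".
- **Who is trained:** "Staff who are a part of the intervention team will only receive this training on the intervention module". In context, this reserves the module for the intervention team.
- **Where the safety guidance is:** the intervention manual covers, among other things, "management of participant distress, confidentiality and safety issues for both staff and participants".
- **Who holds the manual:** "After the training, the trained staff will be provided with the intervention manual".
- **Continuing support:** "an online support centre will be set up for continuous support to the trainers". Befrienders are also monitored through that centre. Nothing equivalent is described for control callers.
- **Control contact** (Control arm: general enquiry phone calls): "They will receive four general enquiry phone calls lasting 5 to 30 min". The main content is COVID-19 psycho-education.

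The Background describes people in socioeconomic hardship as more liable to depression and anxiety, and says that the circumstances of the pandemic can set off self-harm or suicidal behaviour. The Aim also names suicidal behaviour. The Exclusion criteria remove people treated for a mental health condition in the past year, but not people with an untreated one.

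**The concern.** The sentence on control callers does not separate two kinds of training. Befriending technique has to stay out of the control arm, because it is what the trial tests. Recognising acute distress, keeping a disclosure confidential and telling the person where to get help is basic caller conduct, and it need not differ between arms. As worded, the sentence covers both.

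A question about how the family is coping can draw out a disclosure, even in a call mainly about infection precautions. A site that followed the article literally could have a control caller hear such a disclosure with no described guidance on what to do. What is at stake is the care of individual participants. No estimate, test or stated figure changes.

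**Working it through.** **Step 1. Compare what each arm's callers are described as receiving.**

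| Item | Intervention callers | Control callers |
|---|---|---|
| Training | 6-hour virtual session | None specific |
| Distress, confidentiality and safety guidance | In the manual they are given | None described |
| Support and monitoring | Online support centre | None described |
| Calls per participant | 4 | 4 |
| Length of each call | 30 min to 1 h | 5 to 30 min |

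Two details could seem to fill the gap, but neither does. The manual's reference to staff and participants says whose safety it covers; it does not extend the manual to control staff. The confidentiality statement under Data entry and data management concerns de-identified data, not what a caller hears.

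**Step 2. Test the narrower reading.** Suppose the sentence means only that control callers get no befriending training. The described distress guidance is still in the manual, and the manual still goes to trained intervention staff. The asymmetry in the text remains on either reading.

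**Step 3. Size the exposure.** Inputs: 720 control participants (Intervention), 120 participants per agency (Recruitment of participants within PIAs), and 4 calls of 5 to 30 minutes (Control arm: general enquiry phone calls).

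- Calls in all: 720 × 4 = 2880
- Hours in all: 2880 × 5 min = 14,400 min = 240 h, to 2880 × 30 min = 86,400 min = 1440 h
- Calls per control agency: 120 × 4 = 480, or 40 h (at 5 min) to 240 h (at 30 min)
- Per participant: 4 × 5 = 20 min to 4 × 30 = 120 min

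These figures count planned contact, not risk. The article gives no rate of acute disclosure and none can be derived from it, so the number of participants affected is unknown.

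**Step 4. Size the briefing.** Control staffing is not stated. As an assumption, take the befriender load ("Each befriender will be allocated between 10 and 15 students in their PIA") and a briefing of 30 to 60 minutes.

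- Callers per control agency: 120/15 = 8 to 120/10 = 12
- Control callers in all: 720/15 = 48 to 720/10 = 72
- Briefing per control agency: 8 × 0.5 = 4 to 12 × 1 = 12 staff-hours
- Briefing in all: 48 × 0.5 = 24 to 72 × 1 = 72 staff-hours

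Intervention callers can receive the sheet within their existing 6-hour training. If they were briefed separately at the same load, the total would double to 48 to 144 staff-hours.

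**The case against.** The strongest reply is that this is a condensed article. Distress and referral procedures usually sit in the full protocol or the ethics papers, so their absence here proves nothing. That stands, and it is the main reason for the low severity. It does not fully dispose of the point, because the article prints an unqualified rule about control callers and places the guidance it does describe with the other arm.

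A second reply is that the sentence directly follows text on the befriending module, so no befriending training is its natural meaning. That is a fair reading, but Step 2 shows that it does not bring the guidance to control callers.

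A third reply is that a reader might infer that control callers are given no instruction at all. The article does not support that. Their calls have defined content, which implies some instruction, and nothing in the wording forbids a referral sheet.

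A fourth reply concerns the contrast between arms. Crisis strategies belong to Phase 1 of the intervention and linkage with community resources to Phase 3, so a broad referral procedure would move active content into the control arm. A contact inside the trial team would add work that cannot be estimated. That person could also learn the arm of a whole agency, although Design measures to avoid bias says that the team is blind. Both objections are sound, and they determine the form of the fix: acute distress only, and an outside service only.

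**Conclusion.** The point holds as a low-severity, inexpensive improvement to participant safety. As described, control callers have no specific training and no distress, confidentiality or safety guidance, while they make 2880 planned calls (240 to 1440 hours) to people whom the protocol itself treats as vulnerable.

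A reader might go further and conclude that the trial has no safety procedure, that control participants will be harmed, or that the difference in training biases the comparison. The documents support none of these. The full protocol is not shown, no risk is quantified, and keeping befriending skills out of the control arm is a deliberate and proper feature of the design. Sample size, power, significance level and analysis are unaffected.

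The exposure rests on the stated arm size and call schedule. The briefing cost rests on the assumed caller load and briefing length.

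**What to change.** Replace the sentence on control callers with wording such as:

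> Control-arm callers will receive no training in befriending, supportive or problem-solving techniques. They will receive a one-page instruction on recognising acute distress, keeping disclosures confidential, and giving the details of an existing outside crisis or health service.

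Three conditions keep the design intact:

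- **Same sheet, both arms, issued by the research team.** The sheet then does not reveal allocation, and the intervention and control teams stay separate.
- **Acute distress only.** It contains no coping or crisis strategies (Phase 1) and no linkage to jobs or community resources (Phase 3).
- **An outside service, not a trial team member.** The stated blinding is kept and no staff are added.

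If the full protocol already has a procedure that covers control callers, no change is needed beyond applying it to them.

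The cost is one page, its translation (the questionnaires are already to be translated into the local languages, so it can go with them), and a short briefing of about 24 to 72 staff-hours across the control arm on the assumptions above. The downside is a marginally more supportive control call.

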### Intervention

The two arms of the trial are:
Telephone befriending intervention arm (*n*= 720)General enquiry phone call arm (control) (*n*=720)

#### Intervention arm: telephone befriending intervention

The process of enrollment, allocation, follow-up and analysis is demonstrated (Figs. 1 and 2). The intervention involves participants receiving befriending from trained DDU-GKY staff, through one-to-one phone calls which they will receive in their homes, at a convenient time. The telephonic befriending intervention will be conducted in three phases: (i) proactive engagement and crisis intervention, (ii) problem-solving oriented support therapy and (iii) assertive linkage with community resources (see Table 2). The three phases will spread across four phone calls for 30 min to 1-h duration (Figs. 1 and 2). Their telephone support person will contact participants, and an introductory session will be arranged over the phone at each participants’ convenient time to establish a rapport.

**Table 2 Tab2:** Three phases of the structured befriending intervention

Phase	Objectives	Interventions
**Phase 1**: Proactive engagement and crisis intervention	— To provide emotional support — To provide strategies to alleviate distress and crisis	In this session the befriender will: — Establish a positive and supportive relationship with the participant, — Provide emotional support — Psycho-education about COVID-19 including precautionary measures, — Enquire about general health and biological functioning.
**Phase 2**: Problem-solving oriented supportive therapy	— To provide strategies to solve client’s problems	This includes five general stages: — Problem orientation: Helping participant to identify the most distressing problem — Problem definition and formulation: defining the problem based on its impact on day to day functioning — Generation of alternatives: Helping the participant to identify alternative options — Assist the decision-making — Propose strategies to implement
**Phase 3**: Assertive linkage with community resources	— To utilise community resources for the well-being — To solve a crisis like job loss, financial insecurity, etc.	In this session, the befriender will: — Provide practical support and information; — Emphasise on social support and will provide strategies to improve it, — Reassurance to the participant before termination of the session.

**Fig. 1 Fig1:**
[figure not shown]
Schedule of enrolment, interventions and assessment (formatted on the basis of the Standard Protocol Items Recommendations for Interventional Trials [SPIRIT] 2013 template). *WK, week

**Fig. 2 Fig2:**
[figure not shown]
Process of the trial

During the telephone calls, a semi-structured questionnaire will be used to gather information on the stressors and risk factors in the context of this pandemic outbreak. Telephonic conversations will be recorded with the consent of the participants and later transcribed by the research team. The specific domains that will be assessed include the situational stressors in the context of the COVID-19 outbreak and the different support mechanisms available to manage the difficulties. The staff will be trained to encourage the participant to speak about their issues and difficulties in the present context and empathetically listen to their worries.

#### Control arm: general enquiry phone calls

Participants randomised to the control arm will not be receiving any intervention. However, they will participate in a baseline and follow-up assessment using the same instruments. They will receive four general enquiry phone calls lasting 5 to 30 min. It will be a general inquiry about the precautions that are necessary to protect themselves from the infection, and how the family is coping with the lockdown-related issues. The main focus will be given on psycho-education-based inquiries on COVID-19.

### Data entry and data management

The online data collection tool was developed and linked to the dedicated server in the research centre. The participant will enter the data directly to the online mobile portal, uploading the data directly onto the research server. The stored data set and codes will be protected using a password by the trial manager, independent of the trial team. The centrally stored data will be cleaned and analysed by the research team under the supervision of the trial manager, and the trial manager will verify the results independently to ensure the accuracy of the results. Data will be de-identified to ensure the confidentiality of information. Significant findings of the study will be reported in scientific journals and will be presented in conferences and workshops. Interested researchers can contact the principal investigator for further research collaborations.

### Sample size and statistical analysis

A target sample size of 1440 participants (720 in each arm) with less than 5% loss to follow-up after 1 month of intervention is estimated to have 80% power. All participants will be included in the analysis according to their allocated group at randomisation. Statistical tests will use a *p*-value less than 0.05 for significance. All statistical analysis procedures will be done using STATA 14 and R version 3.6.3. Baseline summary statistics (mean, standard deviation, percentage) will be calculated based on groups. Chi-square tests and *T*-tests will be performed to test the significance of the study variables. The odds ratio of the outcome variables for the post-assessment will be calculated using logistic regression modelling and 95% confidence intervals. We will analyse descriptive summaries of socio-demographic aspects and the scores of WHO-5, PHQ-9 and MSPSS as the baseline and after 1 month.

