### Design

Cluster randomised controlled trial

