### Recruitment of clusters (PIAs)

Two project-implementing agencies (PIA) will be recruited from each of the six zones (12 PIAs in total). For a PIA to be included in this study, it should be in one of the six zones and be an active, currently operational PIA with a full-time staff. A list of eligible PIAs will be prepared, and NIRDPR will use a computer-generated randomisation procedure to select the PIAs in the six zones. The NIRDPR will contact only those agencies meeting the inclusion criteria and invite them to participate in the study. This process will be continued till 12 consenting PIAs are selected for the project implementation. Six of the selected PIAs will be allocated to the intervention arm, and 6 PIAs will be allocated to the control arm. The state monitoring agencies will collect information on the number of full-time staff and contact details of students who completed their courses.

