### Recruitment of participants within PIAs

We will recruit 120 passed out youth from each participating PIA (total= 1440). All participants from one PIA will be either in the intervention arm or control arm. The participants are aged between 18 and 35, of all genders, and upskilled in different domains. Participants will be invited to take part in baseline assessment and intervention programmes.

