### Randomisation and blinding

Following the completion of the baseline assessment for all participants, the eligible participants will be randomised at a 1:1 ratio to one of the two arms (intervention or control) by the trial manager based on the PIA to which they belong. A computer technician will create a computer-generated random number list, and odd numbers on the list will be allocated to the intervention arm, and the even numbers will be allocated to the control arm.

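### Twelve agencies are randomised, but the named tests and logistic regression make no allowance for clustering; type I error exceeds 5% by an amount that depends on an ICC the protocol does not give

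*Protocol article*

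**What the plan says.** The Design section of the protocol article reads "Cluster randomised controlled trial". Under Recruitment of clusters (PIAs), two PIAs come from each of six zones, and "Six of the selected PIAs will be allocated to the intervention arm, and 6 PIAs will be allocated to the control arm". Under Recruitment of participants within PIAs, each PIA supplies 120 alumni, 1440 in all, and "All participants from one PIA will be either in the intervention arm or control arm". Randomisation and blinding agrees: participants are placed in an arm "by the trial manager based on the PIA to which they belong". The unit of randomisation is therefore the PIA.

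Sample size and statistical analysis sets the inferential methods. For the outcomes it says: "The odds ratio of the outcome variables for the post-assessment will be calculated using logistic regression modelling and 95% confidence intervals". It also says of chi-square and t-tests that these "tests will be performed to test the significance of the study variables". Significance is judged at p<0.05, and Stata and R are the named software. Neither this section nor any other mentions an ICC, a design effect, a random effect, GEE, cluster-robust errors or an analysis of cluster summaries.

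**The concern.** In their ordinary form, the chi-square test, the t-test and logistic regression take every participant as an independent observation. Alumni of one PIA share an arm and are called by staff of that PIA. The Study location section gives sociocultural and economic variation between settings as the reason for using zones. Some correlation within PIAs is therefore to be expected, and with 120 participants per PIA even a small ICC matters.

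If the section is followed as written, ordinary differences between PIAs count as evidence for or against befriending. The p<0.05 rule would not hold type I error at 5%, and the 95% intervals would cover less often than 95%. This affects all three outcomes that the abstract calls primary: wellbeing, depressive symptoms and perceived social support.

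**Working it through.** **Inputs from the protocol article.** 12 PIAs, 6 per arm; m = 120 per PIA; 720 per arm; less than 5% loss to follow-up; significance at 0.05 (sidedness not stated, two-sided assumed). **Assumed:** the ICC, shown from 0.001 to 0.05.

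**The plan's own figure.** The 80% power cannot be reproduced, because no effect size, SD, event rate or ICC comes with it. It can only be inverted. With 720 independent participants per arm, the difference detectable with 80% power is (1.960 + 0.842) × √(2/720) = 0.148 SD.

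**Type I error of an unadjusted test.** Design effect DE = 1 + (120 − 1) × ICC. The unadjusted standard error is too small by √DE, so true alpha = 2 × [1 − Φ(1.96/√DE)]. The simulations used 4000 null trials per ICC. The logistic case assumed 30% prevalence.

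| ICC | DE | √DE | True alpha, formula | Simulated t-test | Simulated logistic | Simulated t-test on 12 PIA means |
|---|---|---|---|---|---|---|
| 0.001 | 1.119 | 1.058 | 6.4% | 5.5% | 6.6% | 4.4% |
| 0.005 | 1.595 | 1.263 | 12.1% | 12.4% | 12.3% | 5.2% |
| 0.01 | 2.19 | 1.480 | 18.5% | 19.1% | 18.1% | 5.4% |
| 0.02 | 3.38 | 1.838 | 28.6% | 28.1% | 29.7% | 4.6% |
| 0.05 | 6.95 | 2.636 | 45.7% | 45.7% | 46.5% | 5.4% |

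The logistic model is inflated as much as the t-test, while the analysis of PIA means stays near 5%. A 5% loss (m = 114) changes little: 17.9%, 27.8% and 44.7% at ICC 0.01, 0.02 and 0.05.

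**Interval width.** A valid interval must also use a t reference on 12 − 2 = 10 degrees of freedom (critical value 2.228, not 1.960). The width ratio is √DE × 2.228/1.960:
- ICC 0.01: 1.480 × 1.137 = 1.7
- ICC 0.02: 1.838 × 1.137 = 2.1
- ICC 0.05: 2.636 × 1.137 = 3.0

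**If zones are balanced.** Suppose each zone has one PIA per arm and half of the ICC lies at zone level (both are assumptions). Zone variance then cancels from the arm contrast, and DE becomes (1 − ICC) + 120 × ICC/2 = 1.59, 2.18 and 3.95 at ICC 0.01, 0.02 and 0.05. True alpha is then about 12%, 18% and 32%.

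**Power of a valid test.** At ICC 0.01 the standard error of the difference is √(2 × 2.19/720) = 0.078 SD, so 0.148 SD has noncentrality 0.148/0.078 = 1.9. Power on 10 df is about 40%. The same calculation gives 52%, 28% and 16% at ICC 0.005, 0.02 and 0.05.

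**The case against.** The strongest reply is that the article condenses a fuller plan. It never says that observations are treated as independent. Logistic regression can carry a random effect, and a t-test can be run on cluster means. It is right that independence is inferred from the named methods, and a reader should not report it as a declared assumption. But the section is not silent on analysis: it names tests, a model, a threshold and software. A fuller plan would have to replace or modify these methods, not merely fill in detail.

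A second reply is that the chi-square and t-test sentence follows the one on baseline summaries and may concern baseline comparisons only. That is possible. The logistic regression sentence is explicitly about post-assessment outcomes, has the same fault, and is the firmer basis for this point.

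A third reply concerns size. A reader might infer that false-positive rates far exceed 5% in any case. The documents do not support that, because they give no ICC: at 0.001 the error is only 6.4%. Zone balance could lower the figures further, but the protocol does not say whether each zone receives one PIA per arm. A reader might also picture each PIA as one language, one labour market and one staff team, which the article does not state.

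Finally, Study location speaks of 12 PIAs from each zone, which conflicts with two per zone under Recruitment of clusters (PIAs). The total of 12 is supported by the abstract and by 12 × 120 = 1440.

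**Conclusion.** The point holds as a method fixed badly: the analysis named does not match the unit of randomisation. The direction of the error is certain for any ICC above zero. Its size is conditional. Inflation is slight at ICC 0.001, more than double the nominal level at 0.005, and runs from 18.5% to 45.7% over ICC 0.01 to 0.05, or about 12% to 32% under the zone-balanced assumption above. These figures rest on equal clusters of 120, a two-sided test and an assumed ICC.

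A reader might go on to call the 80% power figure wrong. The documents do not allow that conclusion, because its inputs are not given. What can be said is that it is stated without any allowance for clustering. This should be corrected before the data are analysed, since the trial's conclusion on effectiveness depends on these p-values and intervals.

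**What to change.** In Sample size and statistical analysis, replace the participant-level outcome tests with one of these:
- a t-test on the 12 PIA-level means, baseline-adjusted at participant level, with 10 df; or
- a linear mixed model with a random PIA intercept, baseline score and arm, using Kenward-Roger or Satterthwaite degrees of freedom.

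Include zone only if allocation is one PIA per arm within each zone, and state which it is. Fixed zone effects leave about 12 − 1 − 5 − 1 = 5 cluster df, with a critical t of 2.57 against 2.23 on 10 df.

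If odds ratios are kept for dichotomised outcomes, use a cluster-level analysis or a mixed logistic model with a small-sample correction. Moving from odds ratios to mean differences changes what is estimated and should be a stated choice. Do not use uncorrected GEE or sandwich errors with 12 clusters, because they can also reject too often. Report the ICC for each outcome.

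**Cost.** The change is to analysis wording and code, in software already named, with no new data. Intervals will be wider. The 80% power must be restated with an assumed ICC and a stated target difference.

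### The only named effect estimate for three scale scores is a post-assessment odds ratio; a baseline-adjusted mean difference would use data the trial already plans to collect and gain precision

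*Protocol article*

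**What the plan says.** All quotes are from the protocol article.

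- **Effect estimate** (Sample size and statistical analysis): "The odds ratio of the outcome variables for the post-assessment will be calculated using logistic regression modelling and 95% confidence intervals". The text names no cut-point, covariate or adjustment for clustering.
- **Other tests** (same section): chi-square tests and t-tests are planned for the study variables. The outcome, the time point and the estimate they belong to are not given.
- **Baseline scores** (same section): "We will analyse descriptive summaries of socio-demographic aspects and the scores of WHO-5, PHQ-9 and MSPSS as the baseline and after 1 month". This is the only use of the baseline scores that the section states.
- **Outcome scales** (Outcomes; Assessments and procedures): WHO-5 is a score from 0 to 100. MSPSS has 12 items on a 7-point scale. PHQ-9 is scored up to 27, "with scores of 1–4, 5–9, 10–14, 15–19 and 20–27 indicating minimal, mild, moderate, moderately severe and severe depressive symptoms". No band is named as the endpoint, and no threshold is given for WHO-5 or MSPSS.
- **Timing** (Assessments and procedures; Randomisation and blinding): every participant completes all three instruments at baseline, and allocation follows once those assessments are complete.
- **Allocation** (Recruitment of clusters): "Six of the selected PIAs will be allocated to the intervention arm, and 6 PIAs will be allocated to the control arm".

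**The concern.** The hypothesis in the Background is one of degree: fewer depressive symptoms and better mental health. The instruments measure degree. The named effect estimate measures the odds of falling in a category. Two things follow.

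First, categorising a score discards the differences between people on the same side of the cut. The size of the odds ratio also depends on where the cut is placed.

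Second, only twelve PIAs are allocated. Six against six leaves substantial room for the arms to start at different average scores by chance. Where baseline predicts follow-up, part of that difference appears as treatment effect in an estimate that does not adjust for it. The baseline scores precede allocation, so they are valid covariates, and collecting them is already planned.

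**Working it through.** **1. The plan's own figure.** The article puts power at 80% for a total of 1440, split equally between the arms. Follow-up is taken to be nearly complete: "with less than 5% loss to follow-up after 1 month of intervention". The significance level is set as follows: "Statistical tests will use a *p*-value less than 0.05 for significance". It gives no effect size, SD, event rate or ICC, so 1440 cannot be reproduced. Back-solving with two-sided 0.05 (sidedness is assumed) and 720 × 0.95 = 684 analysed per arm, with no clustering:

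d = (1.960 + 0.842) × √(2/684) = 0.15 SD.

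Other inputs fit about as well. For example, d = 0.40 with ICC 0.05 needs N = 1450. The design effect size therefore cannot be identified, and what follows uses assumed values.

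**2. Chance baseline difference between arms.** Inputs: 684 per arm in 6 PIAs, so m = 114 analysed per PIA; the ICC is assumed.

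SD of the difference = √[(2/684) × (1 + 113 × ICC)], in units of the score's SD.

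| ICC | Design effect | SD of difference | 95% range (× 1.96) |
|---|---|---|---|
| 0 | 1.00 | 0.054 | ±0.11 |
| 0.02 | 3.26 | 0.098 | ±0.19 |
| 0.05 | 6.65 | 0.139 | ±0.27 |

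**3. How much carries over.** Assume a baseline to follow-up correlation of 0.5 within and 0.7 between PIAs. The slope of the follow-up PIA mean on the baseline PIA mean is

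(0.7 × ICC + 0.5 × (1 − ICC)/114) / (ICC + (1 − ICC)/114).

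- ICC 0.02: 0.0183/0.0286 = 0.64, so an imbalance of 0.19 SD shifts an unadjusted mean difference by about 0.64 × 0.19 = 0.12 SD.
- ICC 0.05: 0.0392/0.0583 = 0.67, so 0.27 SD shifts it by about 0.67 × 0.27 = 0.18 SD.

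**4. Power under clustering.** Twelve PIAs of 114 were simulated and analysed on PIA-level summaries: proportion above a median split, mean follow-up score, and mean follow-up score adjusted for mean baseline score.

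| d | ICC | Binary, post only | Continuous, post only | Continuous, baseline-adjusted |
|---|---|---|---|---|
| 0.30 | 0.01 | 86% | 93% | 98% |
| 0.30 | 0.02 | 73% | 80% | 92% |
| 0.30 | 0.05 | 47% | 50% | 70% |
| 0.15 | 0.02 | 24% | 29% | 40% |
| 0.15 | 0.05 | 15% | 15% | 23% |

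Closed-form check of the middle column at d = 0.30, ICC 0.02: variance of a PIA mean = 0.02 + 0.98/114 = 0.0286; SE = √(2 × 0.0286/6) = 0.098; 0.30/0.098 = 3.07. On 10 degrees of freedom (critical value 2.23) the non-central t gives about 79%, in line with the simulation. Baseline adjustment lowers the PIA-mean variance to 0.0286 × (1 − 0.64²) = 0.0169, which is where the last column's gain comes from.

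**5. Splitting the gain at d = 0.30.** Keeping the score continuous adds 80 − 73 = 7 points at ICC 0.02 and 50 − 47 = 3 at ICC 0.05. Adding the baseline score gives a further 92 − 80 = 12 and 70 − 50 = 20 points.

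**The case against.** **Cut-points are not forced on every test.** A reader might infer that the whole analysis is dichotomised. It is not: the same section plans t-tests, which can compare continuous scores. This stands. What remains is that the t-tests have no stated outcome, time point or effect estimate, so the odds ratio is the only named measure of effect.

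**Baseline adjustment is not ruled out.** A reader might infer that the plan excludes the baseline scores from the model. The text does not say so. A reference to the post-assessment fixes when the outcome is measured, and an adjusted model has the same outcome. Covariates may be listed in an analysis plan that is not shown here. The article supports only this much: no use beyond description is stated.

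**Cut-points may be fixed elsewhere.** Their absence from a condensed article does not show that they will be chosen after the data are seen. An ordinal logistic model on the PHQ-9 bands would also lose less than a binary split, although WHO-5 and MSPSS would still need categories.

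**Larger losses can be quoted, but they do not fit this design.** For independent, normally distributed scores, a median split keeps about 64% of the information and a cut at 20% prevalence about 49%. An effect with 80% power on the continuous score would then have about 61% and 48%. Those figures ignore clustering. Once variation between PIAs is included, the median-split loss at d = 0.30 is about 3 to 7 points. Nor can the share feeling helpless and depressed in the survey cited in the Background serve as the event rate: it is not a PHQ-9 cut-point, and it comes from another population.

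**The PHQ-9 bands start at 1.** This leaves a score of 0 unclassified, but it is a clerical slip for this purpose. Any split at a higher band boundary puts 0 on the low side.

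**Conclusion.** The point holds as an efficiency improvement at almost no cost. It is not a demonstration that the analysis is invalid. The article ties its only named effect estimate to a categorised outcome, although the primary outcomes are scores, and it states no inferential use for baseline data planned for everyone.

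In the clustered design most of the benefit comes from baseline adjustment: about 12 to 20 power points at d = 0.30 for ICC 0.02 to 0.05, against 3 to 7 for leaving the score continuous. At ICC 0.01 the order reverses (5 against 7), because power is already high. The effect size, ICC and baseline correlations are all assumptions; the article gives none of them. Weaker baseline correlations would shrink the gain.

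The binary figures use a median split of a normal score and PIA-level summaries, so they describe a cluster-respecting analysis. Whether the planned tests account for clustering at all is a separate and larger question. Even a cluster-adjusted odds ratio at post-assessment would leave both parts of this point open.

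**What to change.** In Sample size and statistical analysis:

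1. State the main effect for each outcome as the between-arm mean difference in the continuous score at 1 month, with a 95% confidence interval, adjusted for that score's own baseline value, in a model that accounts for PIA clustering. The article describes no such model, so it has to be written in.
2. Keep any odds ratio as a secondary description, at cut-points for WHO-5, PHQ-9 and MSPSS fixed before analysis.
3. Say which comparison the t-tests and chi-square tests serve, or drop them.

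Zone adjustment is optional. With 12 PIAs, six zones as fixed effects cut the PIA-level degrees of freedom from 12 − 2 = 10 to 12 − 2 − 5 = 5, and the critical t rises from 2.23 to 2.57. If zone is included, that cost should be weighed in advance.

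As a tidy-up, the lowest PHQ-9 band should include 0.

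Cost: a change to the analysis wording. No extra assessment is needed, since all three scores are already planned for every participant at baseline and follow-up. A baseline covariate entered as a PIA mean uses one of the 10 degrees of freedom; the simulated figures already allow for this.
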